### Assessment measures

Information about depression and anxiety symptoms (primary outcome), insomnia, burnout, presenteeism, quality of life, sick leave, consultation about the mental state of the participant and oxidative stress will be collected at baseline, three months, six months (primary time point) and 12 months from registration for each participant (Table 1).

**Table 1 Tab1:** **Schedule for the assessments**

		**Entry**	**7 to 21 days after entry**	**13 weeks from entry (allowing for subsequent 14 days)**	**26 weeks from entry (allowing for subsequent 30 days)**	**52 weeks from entry (allowing for subsequent 30 days)**
Kyoto University	HADS assessed through telephone	x		x	x	x
	Allocation guessed by raters			x	x	x
CRC	Informed consent, registration to EDC, information about allocated group	x				
	Socio-demographic variables (such as age, academic status, marital status and partners)	x				
	Concentrations of omega-3 fatty acids in membrane of RBC, oxidative stress, and antioxidant status	x		x		
		(2 hospitals)		(2 hospitals)		
Participants’ input through EDC	PHQ-9	x		x	x	x
	GAD-7	x		x	x	x
	ISI	x		x	x	x
	MBI	x		x	x	x
	BSI	x	x	x	x	x
	HPQ	x		x	x	x
	EQ-5D	x		x	x	x
	Numbers of incidents and accidents	x		x	x	x
	Numbers of visits to clinics	x		x	x	x
	Numbers of absent days due to any reason	x		x	x	x
	History of taking psychotropic drugs	x		x	x	x
	Adverse events		x	x	x	x

BSI, Bradford Somatic Inventory; CRC, clinical research coordinator; EDC, electronic data capturing; EQ-5D, EuroQol; GAD-7, Generalized Anxiety Disorder 7-item scale; HADS, Hospital Anxiety and Depression Scale; HPQ, World Health Organization Heath and Work Performance Questionnaire; ISI, Insomnia Severity Index; MBI, Maslach’s Burnout Inventory; PHQ-9, Patient Health Questionnaire; PRIME-MD, Primary Care Evaluation of Mental Disorders.

### Primary outcome measure

The primary outcome will be the total depression and anxiety severity changes at week 26 (rated blindly), assessed using the 14-item HADS [32,33] through their mobile phone by a blinded rater located at Kyoto University. All the patients will be requested not to reveal the allocated treatment to the assessors, in order to keep the assessors’ blindness to the groups.

The total score of the HADS (HADS-T) ranges from 0 to 42, with higher scores indicating more symptoms. The HADS has two sub-scores, each ranging from 0 to 21: HADS-D (depression) and HADS-A (anxiety). The defined cutoffs were eight or higher for mild to moderate symptoms and 11 or higher for severe symptoms of anxiety or depression. The reliability and validity of the Japanese version of the HADS has been confirmed, with Cronbach’s alpha values of the scale at 0.79 for the HADS-D and at 0.77 for the HADS-A [22]. The total score will be used as a measure of the severity of depression and anxiety symptoms in the present study.

#### *Secondary outc*o*me measures*

All other self-reported measures will be collected through the EDC system, where the participants can enter their own data at home. Participants will be notified at 13, 26 and 52 weeks to fill in the assessment questionnaires within the following 14, 30 and 30 days through the EDC system, respectively.

### Depression and anxiety symptoms

The HADS will be administered at baseline, 13 and 52 weeks as secondary outcomes, as well as at 26 weeks (the primary outcome).

### Major depressive episode

A current major depressive episode, according to (the Diagnostic and Statistical Manual of Mental Disorders, 4th. Edition (DSM-IV) criteria, will be ascertained using the Primary Care Evaluation of Mental Disorders (PRIME-MD) algorithm in the depression module of the Patient Health Questionnaire (PHQ-9) [23] at baseline, 13, 26 and 52 weeks. The PHQ-9 was developed as a self-report version of the PRIME-MD that aims at a DSM-IV diagnosis of several common mental disorders. The PHQ-9 has been used as an assessment of major depressive disorder, according to DSM-5 [34]. The PHQ-9 consists of the nine diagnostic criteria items, which make a total score range between 0 and 27. Good test-retest reliability (intraclass correlation coefficient (ICC) = 0.92) [35] and internal consistency reliability (Cronbach’s alpha = 0.89) [23] have been reported. The Japanese version has been established through back-translation [36].

### Anxiety

The Generalized Anxiety Disorder 7-item scale (GAD-7) [37] will be used to assess the severity of anxiety symptoms in the participants at baseline, 13, 26 and 52 weeks. The GAD-7 was developed to screen for and evaluate the severity of generalized anxiety disorder (GAD) in the general population. The GAD-7 consists of seven items and can give a diagnosis according to DSM-IV and DSM-5. The internal consistency and test-retest reliability of the GAD-7 were a Cronbach’s alpha of 0.92 and intraclass correlation of 0.83, respectively [37]. Total scores between five and nine, 10 and 14, or 15 and 21 indicate mild, moderate or severe anxiety symptoms, respectively. According to a recently published systematic review, the GAD-7 was the best performing test for GAD, with a positive likelihood ratio of 5.1 (95% CI: 4.3 to 6.0) and a negative likelihood ratio of 0.13 (95% CI: 0.07 to 0.25) [38]. A Japanese version of the GAD-7 has been developed [39] and the agreement rate of diagnosis compared to the Mini International Neuropsychiatric Interview was reported as satisfactory.

### Burnout

The Maslach’s Burnout Inventory (MBI) [40] will be used to assess burnout in nurses. The MBI is a tool for detecting and measuring the severity of burnout syndrome. It is a 22-item questionnaire that assesses the degree of burnout in terms of three subscales: emotional exhaustion (EE), depersonalization (DP) and personal accomplishment (PA). EE represents feelings of being emotionally exhausted and having a lack of energy, DP represents feelings of impersonal responses towards recipients of the service and PA represents feeling of incompetence. The original English version has a good validity and reliability, with a Cronbach’s alpha of 0.71 to 0.90 [41,42]. The Japanese version also has good reliability, with a Cronbach’s alpha of 0.77, 0.76 and 0.60 for EE, DP and PA, respectively [43].

### Insomnia

The Insomnia Severity Index (ISI) [44,45] will be used to assess insomnia at baseline, 13, 26 and 52 weeks. The ISI is now considered a standard global measure for assessing the severity of insomnia and is used in many studies [46,47]. Total scores between eight and 14 and 15 and 28 indicate subthreshold insomnia and clinical insomnia, respectively. The internal consistency of the ISI has a Cronbach’s alpha of 0.90 in a community population [48]. In a clinical population, a difference in score of −8.4 points (95% CI: −7.1 to −9.4) was associated with a moderate improvement, as rated by an independent assessor after treatment [48]. The Japanese version has been validated [49].

### Somatic symptoms

The Bradford Somatic Inventory (BSI) will be used to measure somatic symptoms at baseline, 13, 26 and 52 weeks. The BSI is a 44-item questionnaire for female subjects about symptoms experienced in the previous month, which was designed to detect physical symptoms commonly related to depressed patients [50]. We selected the BSI as a measurement for somatic symptoms because there are no other assessment tools for this purpose in the Japanese language. The original English version of the BSI was translated into Japanese by two Japanese psychiatrists (NW and YM) and back-translated into English by one psychiatrist ([name]). The translations were then checked by the original author of the BSI ([name] [name]). The number of positive items in the BSI will be used as a measure of the severity of somatic symptoms in this study. Data from the BSI will be collected through the EDC on days seven to 21 from entry into the study to check the test-retest reliability.

### Presenteeism

The World Health Organization Heath and Work Performance Questionnaire (HPQ) will be used to assess presenteeism at baseline, 13, 26 and 52 weeks. The HPQ is a self-report instrument designed to estimate the workplace costs of health problems in terms of self-reported reduced job performance (presenteeism). The HPQ measures of presenteeism can be used to calculate two scores: the absolute presenteeism score, obtained by multiplying the respondent’s response to the second question by 10, and the relative presenteeism score, obtained by dividing the first response by the second response, then multiplying by 100. Absolute and relative presenteeism scores will be used in this study.

The validity of the scale has been confirmed in previous studies [51,52]. The Japanese version of the HPQ was used in the World Mental Health Survey in Japan [53]. The area under the curve values for absolute and relative presenteeism in relation to future absences due to mental disease were 0.71 (95% CI: 0.62 to 0.80) and 0.65 (95% CI: 0.55 to 0.75), respectively [54].

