**Methods/Design:**

A factorial-design multi-center randomized trial is currently being conducted. A total of 120 nurses without a managerial position, who work for general hospitals and gave informed consent, have been randomly allocated to a stress management program or psychoeducation using a leaflet, and to omega-3 fatty acids or identical placebo pills. The stress management program has been developed according to mindfulness cognitive therapy and consists of four 30-minute individual sessions conducted using a detailed manual. These sessions are conducted by nurses with a managerial position. Participants allocated to the omega-3 fatty acid groups are provided with 1,200 mg/day of eicosapentaenoic acid and 600 mg/day of docosahexaenoic acid for 90 days.

The primary outcome is the change in the total score of the Hospital Anxiety and Depression Scale (HADS), determined by a blinded rater via the telephone at week 26. Secondary outcomes include the change in HADS score at 13 and 52 weeks; presence of a major depressive episode; severity of depression, anxiety, insomnia, burnout, and presenteeism; utility scores and adverse events at 13, 26 and 52 weeks.

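### The two presenteeism formulas pull in opposite directions on the second response, and no direction of benefit is given for either score

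*Protocol article*

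**What the plan says.** The abstract (Methods/Design) names presenteeism among the secondary outcomes: "severity of depression, anxiety, insomnia, burnout, and presenteeism". The Presenteeism section then fixes two scores from the WHO questionnaire:

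- **Absolute:** "the absolute presenteeism score, obtained by multiplying the respondent’s response to the second question by 10".
- **Relative:** "the relative presenteeism score, obtained by dividing the first response by the second response, then multiplying by 100".

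It adds: "Absolute and relative presenteeism scores will be used in this study". The section describes the questionnaire as an estimate of reduced job performance, so both scores serve one construct. It does not say what the first and second questions ask, what the response range is, or whether a high value of either score is good or bad. Nothing elsewhere in the article corrects the ratio or says that one score is read in reverse.

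Under Data management and analysis, all continuous outcomes at 26 and 52 weeks go into a mixed model for repeated measures. Each is tested at P < 0.05 without correction for multiple tests.

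**The concern.** Both scores depend on the second response, but in opposite ways: the absolute score is proportional to it and the relative score divides by it. An intervention that shifts the second response and leaves the first alone would therefore raise one presenteeism score and lower the other.

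Two scores from one instrument may be oriented differently, provided the plan says so. This one does not. Elsewhere the article does give a direction or anchors: higher HADS totals mean more symptoms, EQ-5D utilities run from death to perfect health, and more positive BSI items mean greater severity.

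If the formulas are coded as written, one of the two results would either be mis-scored or be open to reading with the wrong sign. A real benefit could look like a conflict between the scores, or like harm on one of them. Presenteeism also carries part of the trial's rationale, because the Background section puts its annual cost at 1,346 USD per nurse.

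**Working it through.** **Inputs.** Write F for the first response and S for the second. The Presenteeism section gives

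- absolute score A = 10 × S
- relative score R = 100 × F / S

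The plan states no numerical result for these scores, so there is no figure to reproduce. The response values below are illustrative; the article gives no range.

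**Step 1: direction at a fixed first response.** The slope of A in S is +10. The slope of R in S is −100 × F / S², which is negative for any positive F. With F = 7:

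| S | A = 10 × S | R = 100 × 7 / S |
|---|---|---|
| 5 | 50 | 140 |
| 7 | 70 | 100 |
| 8 | 80 | 87.5 |
| 10 | 100 | 70 |

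R falls strictly as S rises for every fixed F from 1 to 10.

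**Step 2: when the first response also moves.** R falls only if F grows proportionately less than S. Take S from 5 to 6, a ratio of 1.2, starting at F = 7:

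- F rises to 8: R goes from 140 to 100 × 8 / 6 = 133.3, still falling while A rises from 50 to 60.
- F rises to 9: R goes from 140 to 100 × 9 / 6 = 150, and both scores rise.

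So the opposition is strict at a given first response, and conditional otherwise.

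**Step 3: can any reading of the two questions reconcile the formulas?**

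- *S is the respondent's own performance.* An absolute score built on S alone suggests this. A is then sensible, but R has own performance in the denominator. With F = 7 and S going from 5 to 8, A goes from 50 to 80 and R from 140 to 87.5. The ratio is inverted.
- *F is the respondent's own performance and S a comparator.* R is then sensible: with S = 7 and F going from 5 to 8, R goes from 71.4 to 114.3. But A stays at 10 × 7 = 70 and does not respond to own performance at all. The absolute formula uses the wrong item.
- *High responses mean worse performance.* Reversing the polarity changes which end is good. It does not change the opposite movement of A and R in S.

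Under either of the first two readings, one formula is wrong. The only other possibility is that the two scores are meant to be read in opposite directions, which the article does not say.

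**Step 4: after correction.** For an own rating going from 5 to 8 against a fixed 7, the scores should be 10 × own and 100 × own / 7. That gives 50 to 80 and 71.4 to 114.3, rising together. The result is the same whichever question turns out to be the own rating.

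**The case against.** The strongest reply is that the article does not define the questions, so it does not show that the ratio is the faulty part. Multiplying a response by ten does not say whose performance it rates. That stands. A reader might infer that the relative score is simply upside down and should be second over first. The text makes that the more natural reading but does not prove it, because a misprint in the absolute formula would explain the conflict equally well.

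A second reply is that opposite orientation is not in itself an analysis error. The two scores are not combined, and each group difference will be reported with a 95% confidence interval. This is correct as far as it goes, and a plan that stated the two directions would be coherent. This plan states neither, and it presents both scores as measures of the same thing.

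Two stronger readings should be resisted:

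- *That any beneficial intervention must raise one score and lower the other.* Step 2 of the working shows that this depends on how the first response moves. The article gives no data on the two ratings or their correlation, so no correlation between the scores can be claimed for this trial.
- *That the ratio is flawed because the second response could be zero.* The article does not say that zero is allowed, and the reversed ratio would have the same difficulty with the first response. Handling of such values is also the kind of detail an article leaves to the full protocol or SAP.

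Nor can the whole point be left to the SAP. The article chose to state the scoring rule, and the rule as stated is inconsistent.

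**Conclusion.** The point holds in this form: as written, the absolute and relative presenteeism scores move in opposite directions with the second response at a given first response, and no direction of benefit is stated for either. For a first response of 7 and a second response going from 5 to 8, the scores go from 50 to 80 and from 140 to 87.5. The opposition follows from the two formulas alone. Which formula is wrong does not follow from them, and depends on what the two questions ask.

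The reach is limited to one secondary outcome. The primary HADS comparison and the sample size are untouched. It should be corrected before analysis, but it does not threaten the trial's main conclusion.

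**What to change.** Before the presenteeism data are analysed:

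1. Check both formulas against the instrument's scoring guide and identify which question is the respondent's own rating.
2. Correct the formula that is wrong, so that the own rating is the basis of the absolute score and the numerator of the relative score. If the second question is the own rating, the relative score becomes second / first × 100. If the first is, the absolute score becomes 10 × the first response.
3. State for both scores which direction is favourable.

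The cost is a one-sentence correction to the scoring description, a statement of direction, and a matching check of the scoring code. No new data are needed, because only the scoring of the collected responses changes.

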### Quality of life

The EuroQol (EQ-5D) [55] will be used to assess health-related quality of life (QoL) at baseline, 13, 26 and 52 weeks. The EQ-5D is a standardized instrument used as a measure of health outcome and is applicable to a wide range of health conditions and treatments. The five domains include mobility, self-care, usual activities, pain and/or discomfort, and anxiety and/or depression. There are three levels of severity: no problems, some or moderate problems and severe or extreme problems. Each pattern of responses is allocated to an individual utility score, which ranges from 0 (death) to one (perfect health). The Japanese version has been developed [56]. The test-retest reliability of the Japanese version was 0.996, and Cronbach’s alpha was 0.827 [57].

### Oxidative stress

Oxidative stress and antioxidant levels will be evaluated at the baseline and three-month assessments among the nurses working for the National Center of Neurology and Psychiatry Hospital and National Disaster Medical Center. Oxidative stress is the imbalance between oxidative stress and antioxidant defenses. High oxidative stress or low antioxidant status are becoming increasingly recognized as biological mechanisms associated with poor health outcomes and the progression of a wide range of diseases [58,59]. An association between depression and oxidative stress has been reported in a recently published meta-analysis [60]; however, the conclusions seem inconsistent due to large heterogeneity among the included studies, with an I^2^ of 80% and possible selection bias as the studies did not cover a broad range of depression. Moreover, the meta-analysis included only cross-sectional studies; therefore, associations between changes in depression and oxidative stress remain unclear.

In the present study, we will use reactive oxygen metabolite-derived compounds (d-ROMs) and biological antioxidant potential (BAP) tests [61] to evaluate oxidative stress and antioxidant levels, respectively, as used in previous studies [62,63].

### Adverse events

An adverse event is defined as any unwanted or unintended signs (including laboratory exams, suicidal and self-harm behaviors and very unstable mental states), symptoms or disease seen in trial participants, regardless of the causal relationship with the study intervention. Information about any possible adverse events will be collected during the intervention period through the EDC. Participants will be encouraged to input these data via emails at fixed intervals. Information about the severity and degree of adverse events affecting normal life will also be collected. When the severity of severe for adverse events or the degree affecting usual life of moderate or severe due to adverse eventsis presented, the participant will be contacted through telephone or email by a CRC, and termination of the intervention will be discussed.

Adverse events will be classified into major adverse events if they may lead to death or to enduring severe impairment, depending on participants’ conditions and circumstances. Major adverse events shall be reported to the relevant section of the Ministry of Health, Labor and Welfare, as well as to the heads of all research centers and recruiting hospitals.

### Other outcomes

Information about sick leave, consultations on personal mental state and about discontinuation of the allocated interventions will be collected through the EDC.

### Sample size

The sample size was based on a power analysis conducted for the HADS scores. There are no previous reports associated with the stress management program, in terms of nurse-to-nurse interventions, that can contribute to the power calculation of our trial. Based on trials that have used nurses as therapists and the HADS as the primary outcome, one trial has examined the efficacy of cognitive behavioral therapy conducted by nurses for depression in the elderly after lumber fracture operations, and a difference of 3.7 was found compared with treatment as usual [64]. To the best of our knowledge, there have been no reports assessing treatment with omega-3 fatty acids for depression or anxiety in nurses. One systematic review and meta-analysis has shown that treatment with omega-3, ≥60% EPA and ≤40% DHA led to an effect size of −0.026 (95% CI: −0.200 to 0.148), when compared with a placebo [65]. Therefore, the mean difference in the HADS scores was estimated to be 4 ± 6 (SD) between the stress management program and leaflet groups, and between the omega-3 fatty acids and placebo groups. To detect a significant difference at *P* = 0.05 (two-tailed) with a power of 0.9, it was calculated that 48 patients would be required for each of the arms in both comparisons. Thus, allowing for a 20% dropout rate, 60 participants would need to be recruited per group. In the present factorial-design RCT, 30 participants would be necessary for each of the four groups.

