On the other hand, psychological interventions, such as stress management, problem solving and support should be considered as possible interventions in workplace settings because of their feasibility and accessibility. A Cochrane review [17] has revealed that a psychological intervention to alleviate stress among workers in the workplace can be efficacious according to several small RCTs; however, this review concluded that the methodological quality of these trials was not sufficient, and further methodologically sound trials with a larger sample size are needed to reach firm conclusions.

Among the various types of psychotherapy, mindfulness-based cognitive therapy and meditation have been given particular attention by both clinicians and researchers. In a systematic review, mindfulness meditation programs have shown moderate evidence of improvements in depression, with an effect size of 0.30 (95% confidence interval (CI): 0.00 to 0.59) at post-treatment), when compared with nonspecific active controls [18]; however, the review focused on a clinical sample and therefore was not able to conclude any preventive effects of the psychotherapy. To the best of our knowledge, there has been no systematic review focusing on the prevention of depression and anxiety symptoms in the workplace. Although the efficacy of mindfulness-based cognitive therapy in nurses has been examined in a previous RCT [19], the trial included only a small number of participants and no firm conclusions could be drawn. For this reason, a conclusive RCT is necessary to establish evidence of an effective psychological intervention that can help to maintain a healthy mental state in hospital nurses.

Hence, the present study aims to conduct a methodologically rigorous factorial-design trial with 1:1:1:1 allocation to explore the effectiveness of omega-3 PUFAs, and a mindfulness-based stress management program for maintaining a healthy mental state in hospital nurses.

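### The 0.9 power claimed for the omega-3 comparison rests on a 0.67 SD effect that does not follow from the near-zero effect size cited for it

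*Protocol article*

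**What the plan says.** The Sample size section of the protocol article gives one source for each factor.

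- **Stress management:** it says there are no earlier nurse-to-nurse trials to draw on. It takes a trial of nurse-delivered cognitive behavioral therapy in elderly patients after fracture surgery, in which "a difference of 3.7 was found compared with treatment as usual [64"].
- **Omega-3:** it cites a meta-analysis in which preparations with at least 60% EPA "led to an effect size of −0.026 (95% CI: −0.200 to 0.148), when compared with a placebo".

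It then draws a single assumption for both factors: "Therefore, the mean difference in the HADS scores was estimated to be 4 ± 6 (SD) between the stress management program and leaflet groups". The same sentence applies that figure to the supplement factor as well. The design target follows: "To detect a significant difference at *P* = 0.05 (two-tailed) with a power of 0.9", from which "48 patients would be required for each of the arms in both comparisons" and, "allowing for a 20% dropout rate, 60 participants would need to be recruited per group".

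Three other sections bear on this:

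- Supplements interventions gives 1,200 mg EPA and 600 mg DHA, so EPA is 1,200/1,800 = 67% of the two. The trial's product therefore falls in the category to which the cited effect size applies.
- Background reports that omega-3 did not prevent depression in healthy subjects in a recent meta-analysis. It argues that trials at a better dose are still needed, but attaches no effect size to that argument.
- Data management and analysis states a preference for avoiding beta errors over alpha errors, and promises 95% confidence intervals for all group differences.

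**The concern.** The omega-3 assumption is presented as a consequence of the cited evidence, yet that evidence is an effect close to zero with an interval that ends far short of 0.67 SD. Nothing else in the article supplies a basis for 4 points on omega-3. Either the quoted effect size or the inference drawn from it needs correcting.

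At stake is how the omega-3 result will be read. It is one of two co-equal factors, and 0.9 power is claimed for both. A reader who trusts that figure may take a non-significant omega-3 comparison as a 90%-powered negative result for effects of any realistic size. The design has that power only for an effect well outside the cited interval. This also sits badly with a plan that puts avoidance of beta errors first.

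**Working it through.** **Inputs.** From Sample size: difference 4, SD 6, two-sided alpha 0.05, power 0.9, 48 evaluable and 60 recruited per comparison arm, 20% dropout, omega-3 effect size −0.026 (−0.200 to 0.148), nurse-delivered therapy difference 3.7. Allocation is 1:1 at each margin of the factorial.

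**1. Reproduce the plan's figure.** n per arm = 2(1.96 + 1.2816)² × (6/4)² = 2 × 10.508 × 2.25 = 47.3, so 48. With 20% dropout, 48/0.8 = 60, and two margins of 60 give four cells of 30. Power at 48 per arm is 0.904 by the normal formula and 0.898 by the noncentral t. The arithmetic holds.

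**2. Compare the assumption with the citation.** 4/6 = 0.667 SD.

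- Against the point estimate: 0.667/0.026 = 25.6.
- Against the confidence limit further from zero: 0.667/0.200 = 3.3.

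**3. Power at the cited effects.** The two-sided noncentral t was used, with noncentrality d√(n/2) and 2n − 2 degrees of freedom. As a check at d = 0.20 and n = 48: 0.20 × √24 = 0.980, and the normal approximation gives Φ(0.980 − 1.96) + Φ(−0.980 − 1.96) = 0.1635 + 0.0016 = 0.165, against 0.163 from the t.

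| Effect | SD units | Power, 48 per arm | Power, 60 per arm |
|---|---|---|---|
| Assumed 4 points | 0.667 | 0.898 | 0.952 |
| Omega-3 point estimate | 0.026 | 0.052 | 0.052 |
| Omega-3 upper limit | 0.148 | 0.111 | 0.127 |
| Omega-3 lower limit | 0.200 | 0.163 | 0.192 |
| Stress management, 3.7 points (SD 6 assumed) | 0.617 | 0.849 | 0.918 |

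The three omega-3 rows are on the standardised scale, so they do not depend on the SD of 6. The section does not say which sign favours omega-3, so both limits are shown. For scale, 90% power at 0.20 SD would need 2 × 10.508/0.04 = 525.4, so 526 per arm.

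**4. Precision of the omega-3 estimate.** The 95% CI half-width is 1.96 × 6 × √(2/48) = 2.40 points with 48 per arm, and 1.96 × 6 × √(2/60) = 2.15 points with 60. In SD units, 2.40/6 = 0.40, twice the larger cited limit.

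**5. Allowance for a more efficient analysis.** The article gives no baseline correlation. If 6 is the raw SD and adjustment for baseline works through an assumed correlation r of 0.5 to 0.7, the effective effect is 0.20/√(1 − r²) = 0.231 to 0.280. Power at 0.20 SD with 48 per arm then rises to about 20% to 28%. At 0.026 SD it stays near 5%.

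**The case against.** The strongest reply is that a sample size may be built on the difference worth detecting and need not match earlier estimates. The Background also describes the omega-3 literature as mixed, with some reviews positive, and argues for a better dose. That would be a sound defence if the article made it. Instead, the text presents 4 points as following from the citations, and the dose argument carries no effect size.

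A second reply is that −0.026 may be misquoted. The source is not available here, so this cannot be settled. The low power figures therefore hold only if the quoted number is right. The mismatch within the section stands either way.

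A third is that the plan already promises 95% CIs and nowhere equates non-significance with no effect. That is true and it softens the harm, but the unsupported 0.9 remains in the text.

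A reader might also infer more than the documents support:

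- **That the sample size is miscalculated.** It is not: 48 and 60 reproduce.
- **That the stress-management assumption is contradicted to the same degree.** Its closest source gives 3.7 points, and rounding to 4 moves power only from 0.90 to about 0.85. The Background also cites mindfulness programs "with an effect size of 0.30 (95% confidence interval (CI): 0.00 to 0.59) at post-treatment", and 0.67 lies above that upper limit. But that review concerned depression in a clinical sample against nonspecific active controls, and the Background itself says it could not conclude on prevention. It does not cap the effect here.
- **That screening out depressed nurses leaves too little room for a 4-point fall.** The depression exclusion joins a HADS-D threshold and a questionnaire threshold with an and, so meeting one alone does not exclude. Minimization uses a HADS total of 11 or more, so symptomatic nurses are expected. In a prevention trial a difference can also arise from worsening in controls.
- **That any non-significant omega-3 result would be inconclusive.** An estimate near zero with a half-width of 2.4 points would exclude the 4-point target, which is informative.

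**Conclusion.** The concern holds for the omega-3 comparison, as a fault in the basis of the stated power and not in its calculation. The assumed 0.67 SD is about 26 times the cited point estimate and more than three times the larger confidence limit, so the evidence given for it does not support 0.9 power. Provided the quoted effect size is correct, power with 48 evaluable per arm is about 5% at the point estimate, 11% at 0.148 SD and 16% at 0.20 SD. With all 60 per arm it is 5%, 13% and 19%. The 16% and 19% are powers at a confidence limit, not at the cited effect itself. Plausible gains from baseline adjustment do not change the conclusion. For stress management the gap is minor, and its 0.85 rests on applying this protocol's SD of 6 to another trial's difference.

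**What to change.** Rewrite the Sample size paragraph, without enrolling more:

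1. Check the −0.026 and its interval against the cited meta-analysis, and reconcile it with the 4-point assumption.
2. If the figure stands, give the two comparisons separate bases. Describe 4 points as a target difference for omega-3 that is not derived from the cited evidence, and limit the 0.9 power claim to that target. Report omega-3 power at 0.20 SD (about 16%) and 0.026 SD (about 5%), and stress-management power at 3.7 points (about 0.85 if SD 6 applies).
3. State that a non-significant omega-3 result will be interpreted from the observed 95% CI, saying which effects it does and does not exclude, and not as a 90%-powered negative result. The planned half-width is about 2.4 points with 48 per arm and 2.1 to 2.2 with 60.

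The cost is one source check and one reworded paragraph, with a less favourable statement of power for omega-3. Recruitment, allocation, outcome and analysis are unchanged.
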